#### Aerobic training

Aerobic training is performed on a stationary bike (Tunturi Go 50). Table 1 presents the progressions in intensity and duration during the training period, adapted from the American College of Sports Medicine (ACSM) Guidelines for Exercise Testing and Prescription [46]. Exercise intensity is prescribed using percentage of hearth rate reserve (HRR). Participants on medication that attenuates heart rate (e.g. beta-blockers) are prescribed exercise intensity using the Borg Rating of Perceived Exertion (RPE; [47]). The RPE asks participants to rate their subjective feelings of exertion [47]. Heart rate is monitored with the Polar® A300 heart rate monitor. The possibility to increase exercise intensity and duration depends on the individual’s physical ability. Duration, intensity and training load are monitored by a trained research assistant.

**Table 1 Tab1:** Duration and intensity progression of aerobic training

Week	Duration (min)	Intensity (% HRR)	Intensity (RPE)
1&2	20	50–60	12–15
3&4	25	50–60	12–15
5&6	30	60–70	12–15
7–9	35	60–70	12–15
10–12	40	65–75	12–15

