#### Interactive cycling training

The interactive cycling training is a combined cognitive-aerobic bicycle training developed by Fietslabyrint (www.fietslabyrint.nl). Additional file 1 shows the training set-up, in which the home-trainer is connected to a video screen. The aerobic training is identical to the training described above. Additionally, the participants are asked to follow a route through a digital environment presented on the video screen and simultaneously perform cognitive tasks that rely on executive functioning. There are different cognitive training levels and the difficulty of the cognitive tasks increases per level, to ensure that the training remains cognitively challenging. Additional file 2 describes the training tasks in further detail. At the end of each training session participants are provided with feedback on their scores on each task and the scores are registered in a diary. When the participants have a response time of less than 5 s and an error rate of less than 5%, they can proceed to the next level.

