#### Stretching and toning active control group

Stretching and toning consists of relaxation and flexibility exercises with the same duration and frequency as the other training regimes. The exercises require minimal muscle strength and aerobic capacity and are easy to perform. The level of social engagement is similar to the intervention groups. In persons with dementia, social engagement may have a positive effect on cognitive function [48]. The stretching and toning group thus controls for this social effect. The flexibility exercises consist of upper and lower body exercises, including head rotation, shoulder rotation, shoulders up-down, arm rotation, arm and shoulder muscle strengthening, wrist rotations, flexion/extension fingers, rotation hip, stretching hip flexors and extensors, stretching knee flexors and extensors.

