### Statistical analysis

Socio-demographic and clinical characteristics at baseline are presented using descriptive statistics. If group differences are observed at baseline, those variables are included as covariates in further analyses. Alpha is set at 0.05 for all analyses. To assess the effect on the primary and secondary outcome measures, analysis of covariance (ANCOVA) is used with cognitive domain scores on the post-tests/intermediate tests as dependent variables, pre-test scores as covariates and group (interactive cycling, aerobic bicycle training, control) as between subject factor. In an explorative analysis the moderating effect of APOE ε4 is evaluated. All analyses are performed as intention-to-treat analysis, including all participants (irrespective of adherence to intervention). Additionally, analyses are rerun as per-protocol analysis. Missing data are substituted using multiple imputation method. Characteristic variables of the sample and cognitive and physical test scores at the different time points will be included in the imputation model. Each imputed dataset will be analysed, pooled and then reported.

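### The per-protocol rerun reuses the intention-to-treat ANCOVA on a subset selected by adherence, so the cycling-versus-control contrast may be biased, in a direction the protocol does not settle

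*Protocol article*

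**What the plan says.** The Statistical analysis section of the protocol article sets the main approach first: "All analyses are performed as intention-to-treat analysis, including all participants (irrespective of adherence to intervention". The model is an ANCOVA on the post-test or intermediate score, with "pre-test scores as covariates and group (interactive cycling, aerobic bicycle training, control) as between subject factor". There is one other route to covariates: "If group differences are observed at baseline, those variables are included as covariates in further analyses". The supplementary analysis is given in one sentence: "Additionally, analyses are rerun as per-protocol analysis". No separate model is described for it.

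The intervention sections describe different demands:

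- **Both cycling arms.** Table 1 (Aerobic training) rises from 20 min at 50–60% of heart rate reserve in weeks 1 and 2 to 40 min at 65–75% in weeks 10–12. The text adds: "The possibility to increase exercise intensity and duration depends on the individual’s physical ability".
- **Interactive arm.** Participants do the same aerobic work and also "simultaneously perform cognitive tasks that rely on executive functioning".
- **Control arm.** "The exercises require minimal muscle strength and aerobic capacity and are easy to perform".

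Session frequency and programme length are the same in all three arms (Interventions and control condition).

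**The concern.** Randomisation makes the three groups comparable as randomised. Once participants are kept or removed because of what they did during training, that protection is lost, and the comparison depends on whether the model accounts for why people were removed.

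Here the arms ask for different things. Physical fitness, mobility and frailty could plausibly affect who keeps to a progressive cycling programme more than who keeps to light stretching. If those traits also relate to the 12-week executive score beyond the pre-test score, the retained groups differ in prognosis and the ANCOVA attributes the difference to training. The pre-test executive score does not stand in for fitness or frailty. The baseline-difference rule brings in a variable only if it happens to be imbalanced between groups; it does not target predictors of adherence.

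What is at stake is interpretation. A per-protocol estimate larger than the intention-to-treat one could be taken as a dose effect when part of it is selection. A smaller one could be misread in the opposite way.

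**Working it through.** The protocol gives no figure for the per-protocol analysis, so there is nothing of its own to reproduce. It gives no adherence by arm, only 15% expected drop-out overall (Sample size). All exclusion rates and correlations below are assumptions.

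**Inputs**

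- p: proportion excluded in an arm (assumed).
- r: correlation of the tendency to adhere with the outcome residual, that is, the 12-week score after adjustment for pre-test (assumed).
- Pre-post correlation 0.6 (assumed), used to convert residual SD to outcome SD.
- d = 0.50 (Sample size), as a yardstick only.
- 57 per arm in the simulation: 171 / 3, with equal allocation assumed.

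**Formula.** If the least adherent fraction p is removed, the mean residual among those retained shifts by r × φ(z_p) / (1 − p), where φ is the standard normal density and z_p its p-quantile. The bias, under no true effect, is the cycling shift minus the control shift.

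**Illustrative case, 30% v 10% excluded, r = 0.3**

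- Cycling: 0.3 × 0.3477 / 0.70 = 0.149
- Control: 0.3 × 0.1755 / 0.90 = 0.0585
- Difference: 0.091 residual SD
- In outcome SD: 0.091 × √(1 − 0.6²) = 0.091 × 0.8 = 0.073, about 0.07
- Against d = 0.50, if that is in outcome SD: 0.073 / 0.50 = about 15%

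Dividing 0.091 directly by 0.50 would give 18%, but that mixes residual and outcome SD.

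**Range (cycling minus control, residual SD)**

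| Excluded, cycling v control | r | Bias |
|---|---|---|
| 15% v 15%, or 30% v 30% | any | 0 |
| any | 0 | 0 |
| 20% v 10% | 0.2 | +0.03 |
| 15% v 5% | 0.2 to 0.3 | +0.03 to +0.05 |
| 30% v 10% | 0.4 | +0.12 |
| 30% v 5% | 0.2 to 0.3 | +0.08 to +0.12 |
| 30% v 5% | 0.5 | +0.19 |
| 15% v 25% | 0.2 to 0.3 | −0.03 to −0.05 |

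**Simulation check.** One cycling arm was compared with control by ANCOVA on the pre-test score, with no true effect, 57 randomised per arm, pre-post correlation 0.6 and 4,000 runs. Estimates are in outcome SD; the nominal rejection rate is 5%.

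| Excluded, cycling v control | r | Mean estimate | Rejected |
|---|---|---|---|
| 15% v 15% | 0.3 | 0.00 | 5.4% |
| 15% v 5% | 0.2 | +0.02 | 4.6% |
| 30% v 5% | 0.2 | +0.06 | 6.6% |
| 30% v 5% | 0.3 | +0.09 | 8.8% |
| 30% v 5% | 0.5 | +0.16 | 16.7% |
| 15% v 25% | 0.3 | −0.03 | 6.1% |

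The formula and the simulation agree: at 30% v 5% and r = 0.3, 0.116 residual SD × 0.8 = 0.093 outcome SD, matching the simulated +0.09. Adjusting for the pre-test score does not remove the shift, because here selection acts on the part of the outcome that the pre-test score does not explain.

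**The case against.** A reader might infer that the rerun compares selected, fitter cyclists with nearly unselected controls and so favours cycling. The protocol does not support that reading:

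- It reports no adherence by arm and no rule for the per-protocol set. Nothing says that intensity or duration reached will define it. The cut-off may properly sit in the full protocol or analysis plan, and its absence here is no fault.
- Attendance burden is equal by design, and sessions are individually guided in every arm.
- Cycling progression is tailored to ability and intensity is relative to the person, so a frailer cyclist who does not progress may still be on protocol. People with comorbidities that limit physical activity are excluded at entry.
- The bias can be zero or run against cycling, as the working shows.

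The argument also bears less on one comparison. The aerobic component is identical in the two cycling arms, so selection on fitness largely drops out of combined versus single aerobic training. Only the added cognitive tasks could select differently there.

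Finally, the rerun is already supplementary to intention-to-treat, and nothing presents it as confirmatory or as evidence of a dose effect. It could be said that what is left applies to any per-protocol analysis.

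Most of this stands and limits the point to a conditional one. It does not answer the remaining issue: the model the article states for this subset adjusts for no named predictor of adherence, the arms differ in demand on the article's own description, and suitable baseline measures are available.

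**Conclusion.** The point holds in conditional form and is minor. The supplementary per-protocol comparison of cycling with control may be biased, because the same ANCOVA is applied after selection on adherence and the arms differ in what they demand. Neither the direction nor the size can be read from the protocol. Under the illustrative assumptions (30% v 10% excluded, r = 0.3) the shift is about 0.09 residual SD, or about 0.07 outcome SD with a pre-post correlation of 0.6. Across the other assumed scenarios it runs from −0.05 to +0.19 residual SD, and it is zero with equal adherence or no link to prognosis. The intention-to-treat result, which carries the trial's inference, is not affected.

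**What to change.** Keep the intention-to-treat analysis as it is. For the per-protocol model only, prespecify a short list of baseline predictors of adherence and prognosis and add them to group and pre-test score. Candidates already collected are Åstrand fitness, Timed Up & Go or the 10-m walk, the frailty index and the MMSE score. Include them whether or not they differ between groups at baseline. Beside the result, show the number excluded and the reasons in each arm; reasons for missed sessions are already recorded by the trainers.

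The cost is a change of wording and a few degrees of freedom, with no new data collection. Adjustment reduces selection bias to the extent that these variables capture it and cannot guarantee its removal, so the exclusions by arm are needed for the reader to judge what may remain.

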## Discussion

Dementia is highly prevalent among older adults. To date no effective disease modifying treatment exists [4]. Combined cognitive-aerobic training seems to be a promising intervention to slow the rate of dementia related cognitive decline. However, up to now, there is insufficient evidence to support its effectiveness. To the best of our knowledge, our study is the first to evaluate the effect of a combined cognitive-aerobic bicycle training and a single aerobic bicycle training on executive functioning in older adults with mild dementia.

One of the major strengths of this study is the design with three groups. Most previous training studies compared a combined cognitive-aerobic training or a single aerobic training with a control group. This study includes both a combined cognitive-aerobic training and a single aerobic training. This gives us the opportunity to assess the differential effects between both training conditions and therewith identify the effectiveness of the different components of the intervention. Another strength is that the difficulty level of the cognitive component in the combined cognitive-aerobic training is adapted to the performance level of the participant. This insures that the training remains cognitively challenging.

A limitation of this study is the relatively short duration of the trial. Previous randomized controlled trials showing cognitive benefits of physical activity or combined cognitive-physical training in older adults with dementia, had intervention periods of 12 weeks or more [7, 33]. We chose an intervention period of 12 weeks to increase the feasibility and adherence rate and minimize drop-out. Another limitation of this study is that the research population is very heterogeneous as older adults with different types of dementia (Alzheimer, vascular or mixed type) are included. This may affect the internal validity of the study. However, the heterogeneous population will increase the external validity of the results of this study to the community dwelling dementia population.

## Conclusions

The results of this study will provide an important contribution to the existing body of knowledge on combined cognitive-aerobic interventions and single aerobic interventions in older adults with dementia. The results of this study can be important for physical and mental activity recommendations in older adults with dementia.

## Abbreviations

ACSM: American College of Sports Medicine
AD: Alzheimer’s disease
ANCOVA: Analysis of covariance
APOE: Apolipoprotein E
HR: Heart rate
HRR: Heart rate reserve
MMSE: Mini-mental status examination
PCR: Polymerase Chain Reaction
RCT: Randomised controlled trial
RPE: Rate of perceived exertion
TOPICS-MDS: The Older Persons and Informal Caregivers Survey Minimum DataSet
WAIS: Wechsler Adult Intelligence Scale
WMS: Wechsler Memory Scale
